#### Costs

For the economic evaluation a short questionnaire will be used based on the original TiC-P questionnaire (30). The questionnaire includes questions regarding health care utilization, work absenteeism and presenteeism. Additionally, information regarding medication use is derived from the pharmacy of the participant. The costs of the lifestyle program will be measured using a bottom-up approach.

#### Economic evaluation

Both a cost-effectiveness analysis (CEA) and a cost-utility analysis (CUA) will be performed from a societal perspective. Missing cost and effect data will be imputed using Multiple Imputation with Chained Equations (MICE) according to the MICE algorithm developed by Van Buuren [29]. In addition, incremental cost-effectiveness ratios (ICERs) will be calculated. Bias-corrected and accelerated bootstrapping with 5000 replications will be used to estimate statistical uncertainty surrounding the ICERs. Uncertainty surrounding ICERs will be graphically presented on cost-effectiveness planes.

A budget impact analysis (BIA) will be conducted from the perspective of health-care decision makers. Perspectives that will be considered are the societal and the government (Budget Kader Zorg) perspective. Different scenarios will be evaluated including the following: 1) the lifestyle intervention is not implemented, i.e., all patients receive usual care, 2) the intervention is offered to the whole patient population, 3) the intervention is implemented over a 4 years period (25% of the patient population per year), and 4) the intervention is only offered to specific subgroups of the potential patient population. One-way sensitivity analyses will be performed in which the adoption rate of the lifestyle intervention and the impact on long-term clinical outcomes will be varied.

#### Process evaluation

A process evaluation will be performed in order to identify barriers and facilitators of the SMILE program and experiences of FACT team members with the delivery of the training and intervention. This will be done by organizing focus groups and/or semi-structured interviews with both clients and trained mental health care workers. An overview of the SMILE measurements, instruments and data collection schedule is provided in Table 1.

**Table 1 Tab1:** SMILE measurements, instruments and data collection schedule

	Baseline	3 month	6 month	12 month
PRIMARY				
Weight loss (kg)	x	X	x	x
CLINICAL OUTCOMES				
BMI (kg/m^2^)	x	X	x	x
Waist circumference (cm)	x	X	x	x
Lipid profiles*	x			x
Glucose metabolism (mmol/l)	x			x
Systolic BP (mm/hg)	x		x	x
Diastolic BP (mm/hg)	x		x	x
PATIENT REPORTS				
Quality of life (SF12 and EQ-5D-5 L)	x		x	x
Health related self-efficacy (PAM-13)	x		x	x
Self-reported views on physical activity, nutrition status and sleep	x		x	x
Smoking status	x		x	x
DEMOGRAPHICS				
Age, gender, ethnicity	x			
Education level	x			
Marital status	x			x
Employment status	x			x
Diagnosis of SMI	x			
Number of years receiving ambulatory mental care	x			
COSTS				
Health care utilization and lost productivity questionnaire	x		x	x
Medication use	x		x	x
OTHER				
Compliance to group sessions	Weekly /monthly			

*Lipid profiles include fasting cholesterol (HDL, LDL, total) and fasting triglycerides (mmol/l)

### Sample size

This trial is powered to detect a mean difference of 4 kg in weight reduction after 1 year between the intervention and usual care group [15, 30]. Using a power of 0.80 and an alpha of 0.05, two groups of 100 participants are needed to detect a difference of 4 kg. Assuming an ICC of 0.01 and a dropout rate of 20% [15, 30, 31], we aim to recruit 260 participants in total.

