## Methods

### Study design

We will perform a pragmatic multi-centre cluster randomized controlled trial including an economic evaluation from a societal perspective. Follow-up will be 1 year.

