### Setting

We will recruit approximately 18 FACT-teams from different mental health care organisations throughout different regions in the Netherlands. To recruit these FACT-teams, we will approach several teams with brief information about the study. If a FACT-team is interested in the study, research staff will provide a presentation for all the members of the FACT-team. Based on this presentation, teams will decide if they are interested in joining the study or not. All FACT-teams will have be certified as “FACT” by the Certification Center ACT and FACT at the beginning of the study.

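### The recruitment target of 260 does not follow from the protocol's own sample-size inputs; the consistent figure is about 276 to 279, a small under-sizing

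*Protocol article*

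**What the plan says.** The Sample size section of the protocol article sets the target effect: "This trial is powered to detect a mean difference of 4 kg in weight reduction after 1 year". The error rates follow ("Using a power of 0.80 and an alpha of 0.05"), and the requirement before any inflation is that "two groups of 100 participants are needed to detect a difference of 4 kg". The next sentence brings in clustering and attrition together and gives the recruitment figure: "Assuming an ICC of 0.01 and a dropout rate of 20% [15, 30, 31], we aim to recruit 260 participants in total".

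The section gives no standard deviation, cluster size or design effect. The number of clusters is in the Setting section: "We will recruit approximately 18 FACT-teams from different mental health care organisations". The Abstract gives the same approximate number of teams.

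**The concern.** The paragraph presents 260 as the result of inflating 200 for an ICC of 0.01 and 20% dropout. With about 18 teams, average team size is well above ten, so even this small ICC adds roughly 10% to the requirement. Dropout of 20% then adds a further 25%, because the number is divided by 0.8. The step from 200 to 260 is a 30% increase, which is less than the two adjustments together require.

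What is at stake is the accuracy of the power statement for the primary outcome. A reader of a null result will take from it that a 4 kg difference would have been detected with 80% probability under the stated assumptions.

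**Working it through.** **Inputs**
- From the Sample size section: 4 kg, power 0.80, alpha 0.05 (taken as two-sided; the text does not say), 100 per group (200 in total), ICC 0.01, dropout 20%, target 260.
- From the Setting section: about 18 teams, taken as equal in size.

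**Step 1. The 100 per group**

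The SD is not stated, so it has to be inferred.
- Normal approximation: SD = 4 / [(1.960 + 0.842) x sqrt(2/100)] = 10.1 kg.
- Two-sample t-test with SD 10 (standardised effect 0.4): 99.08 per group, which rounds up to 100.

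So 100 per group is coherent as an unclustered calculation with an SD of about 10 kg. The documents do not settle whether it was 10 or 10.1, so both are carried forward.

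**Step 2. What 260 delivers**
- Completers: 260 x 0.80 = 208.
- Completers per team: 208 / 18 = 11.56.
- Design effect: 1 + (11.56 - 1) x 0.01 = 1.106.
- Effective sample size: 208 / 1.106 = 188, against the 200 needed.

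**Step 3. What the inputs require**

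Required total = 200 x design effect / 0.8. The answer depends slightly on which team size enters the design effect:

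| Team size used | Design effect | Analysed | Recruited |
|---|---|---|---|
| 200/18 = 11.11 | 1.101 | 220.2 | 276 |
| 208/18 = 11.56 | 1.106 | 221.1 | 277 |
| 18 teams fixed, solved for consistency (12.4) | 1.114 | 222.75 | 279 |

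For the last row, with k teams the analysed number is 200 x (1 - 0.01) / (1 - 200 x 0.01/k). At k = 18 this is 198 / 0.8889 = 222.75, and 222.75 / 0.8 = 278.4.

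**Step 4. Does the word "approximately" rescue it?**

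Using the same formula, the recruitment requirement is 283 with 16 teams, 275 with 20, about 272 with 22 and 270 with 24. It falls to 260 only at about 42 teams. Put the other way, 208/200 = 1.04 is the largest design effect that 260 can absorb, which means 5 completers per team. With 18 teams, 260 would allow dropout of 1 - 222.75/260 = 14%, not 20%.

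**Step 5. Where 260 could come from**
- Ignoring clustering: 200 / 0.8 = 250.
- Dropout as a multiplier of 1.2: 200 x 1.10 x 1.2 = 264.
- Adding the two allowances: 200 x (1 + 0.10 + 0.20) = 260.

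The additive route matches exactly. That it was the route used is an inference.

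**Step 6. Power at 260**

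Standard error = SD x sqrt(4/188.1); power = Phi(4/SE - 1.960); detectable difference at 80% power = 2.802 x SE.

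| SD (kg) | SE | 4/SE | Power for 4 kg | Difference at 80% power |
|---|---|---|---|---|
| 10 | 1.458 | 2.743 | 78.3% | 4.09 kg |
| 10.1 | 1.473 | 2.716 | 77.5% | 4.13 kg |

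**The case against.** The strongest reply is that the effect is small and that a two-mean formula does not settle the power of the planned analysis. The Statistical analysis section plans intention-to-treat linear mixed models with correction for prognostic variables, and Table 1 schedules weight at baseline, 3, 6 and 12 months. Participants who drop out after an interim weight can still contribute, and adjustment can recover precision. This stands as a limit on the conclusion: a reader might infer that the trial falls short of 80% power, but the documents do not establish that for the mixed model. It does not repair the arithmetic, because the Sample size section invokes neither adjustment nor a correlation.

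It can also be said that 18 is approximate and is not given as an input to the calculation. That is true, but no count from 16 to 24 teams brings the requirement down to 260. Nor does it help to suppose that the 200 already includes clustering: 200 / 0.8 is 250.

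Three stronger readings are tempting and should not be drawn:
- **A shortfall of 24 and power of 76.5%.** Using enrolled team size (260/18 = 14.4) in the design effect gives a requirement of 284. But that mixes enrolled team size with a count of completers. On completers throughout, the figures are those in the working.
- **Power near 72%.** A t reference on 16 cluster-level degrees of freedom gives about 72 to 73% at 260. Most of that drop comes from the choice of degrees of freedom, since a full effective sample size of 200 would give only about 75 to 76% on the same basis. The protocol does not specify that choice, and it is separate from this arithmetic.
- **An SD of 10.1 kg.** This is only what the normal approximation returns. An SD of 10 with a t-test also gives exactly 100 per group.

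Power at higher ICC values likewise tests a different assumption and says nothing about whether 260 follows from 0.01.

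**Conclusion.** The point holds as an arithmetic inconsistency of minor severity. The stated inputs with about 18 teams require about 276 to 279 recruits, so 260 is short by 16 to 19 participants, or 6 to 7% of the stated target. By the simple two-mean calculation, power for 4 kg is about 78% (77.5 to 78.3%) instead of 80%, and 80% power is reached at about 4.1 kg. A loss of about two points would hardly change how a null result is read.

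This rests on a two-sided test, 18 teams of equal size, dropout of exactly 20%, analysis of completers, and an inferred SD of 10 to 10.1 kg. Unequal team sizes would lower power somewhat; covariate or repeated-measures adjustment could raise it.

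**What to change.** Keep 260 and restate the Sample size paragraph so that a reader can reproduce it. Give:
- the SD actually used, from the sponsor's own calculation and not back-solved;
- the number of teams assumed and the completers per team (about 11.6 with 18 teams);
- the design effect of about 1.11;
- dropout applied as division by 0.8;
- the resulting power, about 78% for 4 kg, or 80% for about 4.1 kg.

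If the sponsor relies on baseline or repeated-measures adjustment to reach 80%, the paragraph should say so and give the correlation assumed.

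The cost is wording only. The stated power becomes slightly less favourable; recruitment, design and analysis do not change.

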### Statistical analysis

Baseline demographic characteristics of the participants in the intervention and control group will be presented using descriptive statistics (mean (standard deviation), median (range) or (proportion)).

All analysis will be on an intention-to-treat basis. Multivariable analyses techniques will be used to correct for prognostic variables. To study the effectiveness of the lifestyle intervention versus usual care in reducing weight, linear mixed models will be used. We will examine between-group differences for various conceptualizations for the primary outcome weight, including percentage weight change, the proportions of people with SMI who lose at least 5 and 10% of their baseline weight. Also, linear and logistic mixed models (depending on the outcome) will be used to test the differences between both groups regarding the secondary clinical outcome parameters; waist circumference, lipids, blood pressure and glucose. Furthermore, we will examine whether there was an effect of the intervention on patient reported outcomes, including perceived health, quality of life and health related self-efficacy. For this purpose, we will also use linear mixed models. Next, we will evaluate whether dose, defined as the number of intervention sessions, is related to change in the outcomes across time among participants who receive the intervention.

Finally, in case of unequal distributions of demographic variables between the two treatment groups, multivariate analyses techniques will be used to correct for these differences.

## Discussion

Research suggest lifestyle interventions can be effective in improving physical health of people with SMI. However, there is currently no evidence of cost-effectiveness regarding a lifestyle intervention for people with SMI in a Dutch outpatient setting. Because lifestyle interventions are typically intensive and include many group and individual sessions, the costs of these programs are substantial. Given the limited healthcare resources it is of utmost importance to evaluate whether the additional costs are worth the effects. Given the large number of persons with SMI and cardiovascular risks, and the associated high burden for the patient, family members and society, this study is a matter of urgency. This paper presents the design of a cluster randomized controlled trial to evaluate the effectiveness and cost-effectiveness of a lifestyle intervention for people with SMI in the Dutch outpatient psychiatric treatment setting.

The SMILE intervention is primarily modelled after the STRIDE intervention [14], developed for persons with SMI and effective in reducing weight and cardiovascular risk factors [15]. The SMILE intervention will be carried out by trained mental health nurses working in FACT-teams in the Netherlands. It is hypothesized that the SMILE intervention is more effective than usual care in reducing weight, reducing cardiovascular risk factors, improving quality of life. Although the costs of the intervention will be higher than usual care, these costs might be outweighed by lower costs of other healthcare utilization and increased productivity. This study has substantial societal value as it provides financing organizations and governments with better insights how to spend the available resources in the most efficient way.

A strength of the current study is its pragmatic design. A large number of studies, specifically randomised controlled trials, use highly controlled settings which could greatly differ from regular care. In the current study, the intervention is implemented by mental health care workers from FACT-teams in the current regular care situation, with the same available time, priorities, and motivation. This pragmatic design will enhance the generalizability of the study results and therefore the possibilities to implement the SMILE intervention in a real-life mental health care setting.

The intervention is based on motivational interviewing techniques and the behavior change theories. Both are very important in order to stimulate behaviour change [32–34]. As participants formulate their own personal goals each week, they can tailor their goals to their personal needs, capabilities and motivation at that moment. However, as Dutch and U.S. mental health care differ to a certain extent, the effect of the adapted STRIDE intervention may differ within Dutch mental health care. We believe that even though the characteristics of the healthcare system differ between countries, the core principles of behaviour change are the same in each country and the difference in characteristics is not likely to have a major impact on the results of this study.

A few adaptations of the STRIDE interventions were made in order to implement the study according to practical possibilities of current mental health care and to fit Dutch guidelines and food customs [35, 36]. One of the adaptations was that the SMILE study will focus less on calorie counting. Reducing calories and monitoring is one of the core intervention components of STRIDE. Calorie density of food products is still an important topic within the group sessions, but the counting of calories is less emphasized. Furthermore, group leaders will not be able to evaluate nutrition, physical activity and sleep journals of the participants for each group session. We chose not to implement this in the intervention, as this would be too time consuming for group leaders. Such evaluations will be integrated within the “check-in” part of the 2-h group session, where progress is discussed and evaluated.

Overall, the SMILE intervention for persons with SMI will provide important and relevant information on the effectiveness, cost-effectiveness, feasibility and delivery of a lifestyle intervention in a Dutch outpatient treatment setting. The first results of this study are expected in 2020.

## Abbreviations

BMI: body mass index
CEA: Cost-Effectiveness
FACT: Flexible Assertive Community Treatment
ICERs: Incremental Cost-Effectiveness ratios
PAM 13: patient activation measure 13
SF12: Short form 12
SMI: serious mental illness
SMILE: Serious Mental Illness Evaluation Lifestyle Evaluation
